## Procedures by main study phases

### Pre-treatment period

#### Screening visit (Visit 1) (Week -1 to –4)

Having given consent, subjects will undergo screening assessments to determine whether they are eligible to participate in the study according to the criteria listed in Section 5.2 and Section 5.3. The following evaluations will be performed during screening:

- Review of inclusion/exclusion criteria
- Medical/surgical history (including current disease, pre‑ART CD4 counts, and pre‑ART HIV-1 viral load)
- Physical examination (including height)
- Vital signs (blood pressure, heart rate)
- Clinical chemistry and hematology (hemoglobin, CRP, WBC, platelets, creatinine, Na, K, AST, ALT, LDH, ALP, -GT, albumin, total bilirubin, 2-microglobulin).
- Viral load (HIV-1 RNA) andCD4 counts
- T cell responses.
- Concomitant medications and AEs

At the investigator’s discretion, laboratory tests may be ordered through the local laboratory to confirm a subject’s current status regarding chronic active infections or AIDS related illnesses in order to confirm eligibility in the trial if the status is not sufficiently documented in the subject’s medical records.

***Randomization:*** When the results of the screening evaluations are available to confirm eligibility the subjects will be randomized.

### Treatment Period

The treatment period consists of a 4-week period with four weekly administration of study drug, beginning at day 1.

#### Visit 2 (Week 1 - Day 1)

This visit will occur at least five days but not more than 28 days after the screening visit. The following procedures will be performed in the following order (it is important that all blood samples are taken before drug administration):

- Review of concomitant medications and AEs
- Physical examination, including weight
- Vital signs
- Clinical chemistry and hematology and optional HLA type
- Viral load (HIV-1 RNA) and CD4 counts
- T-cell responses
- Collection of mucosal sections
- Collection of urine
- Administration of study drugs via intranasal administration

The subject should remain in the clinic for 30 min after the administration of study drug to be monitored for adverse reactions to the immunization.

#### Visit 3 (Week 2 – Day 8(1))

The following procedures will be performed in the following order:

- Review of concomitant medications and AEs
- Administration of study drugs via intranasal administration
- T-cell responses (optional)

The subject should remain in the clinic for 30 min after the administration of study drug to be monitored for adverse reactions to the immunization.

#### Visit 4 (Week 3 – Day 15 (1))

The following procedures will be performed in the following order:

- Review of concomitant medications and AEs
- Administration of study drugs via intradermal injection
- T-cell responses (optional)

The subject should remain in the clinic for 30 min after the administration of study drug to be monitored for adverse reactions to the immunization.

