# Study objectives AND ENDPOINTS

## Study objectives

### Primary objective

The primary objective of this study is to evaluate the safety of intranasal administration of Vacc-4x with Endocine as adjuvant at three different dose levels.

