## Study endpoints

### Safety endpoints

- AEs recorded at each scheduled and unscheduled visit
- Clinical laboratory evaluations (clinical chemistry, hematology) at screening, week 1, week 4 and week 8 (Termination).
- Viral load (HIV-1 RNA) at screening, week 1, week 4 and week 8 (Termination).
- Physical examinations at screening, week 1, week 4 and week 8 (Termination).
- Vital signs (heart rate, blood pressure) at screening, week 1, week 4, and week 8 (Termination).

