# study design

## Overall study design and flow chart

The study is a single-blinded, sequential design, single centre pilot study in HIV-positive subjects on treatment (ART). Twenty-four subjects will be enrolled into one of four treatment groups.

| **Group** | **Treatment** | **No. of subjects in Europe** |
| --- | --- | --- |
| 1 | 80 µg Vacc-4x + Endocine* | 6 |
| 2 | 400 µg Vacc-4x + Endocine* | 6 |
| 3 | 1.2 mg Vacc-4x + Endocine* | 6 |
| 4 | Endocine* | 6 |

* adjuvant

Subjects who have been HIV-positive and stable on ART for the last 6 months and CD4 cell counts ≥400x 10 6 /L and who meet the other inclusion and exclusion criteria will be eligible for the study. The duration of the main study is 8 weeks plus a screening period of up to 4 weeks. A study flow chart is presented in Table 2.

Table 2 Study Flow Chart

| **PARAMETERS** | **Weeks**  **Day** | **-4** | **1 2 3 4**  **1 8 15 22** | | | | | **8 END**  **50-53 (DTH)** | | |
| --- | --- | --- | --- | --- | --- | --- | --- | --- | --- | --- |
| Visits | 1 | 2 3 4 5 | | | | |  | | |
|  | Scree-ning | Immunization  period | | | | | | Follow-up  period | |
| Randomization | | x |  |  |  |  |  |  | |  |
| Immunizationa)  VACC-4x / Endocine | |  | x | x | x | x |  |  | |  |
| DTH-test b) | |  |  |  |  |  |  |  | | x |
| Adverse event | |  | x | x | x | x |  |  | | x |
| Vital signs/Physical examinationc) | | x | x |  |  | x |  |  | | x |
| Blood sample:  general safety d) | | x | x |  |  | x |  |  | | x |
| Blood sample:  Viral load (HIV-1 RNA), CD4 | | x | x |  |  | x |  |  | | x |
| Blood sample:  T-cell responsee) | | X | X | x | x | X |  |  | | X |
| Sampling of mucosal secretions | |  | x |  |  | x |  |  | | x |
| Urine sample | |  | x |  |  |  |  |  | | x |
| Inclusion/Exclusion | | x |  |  |  |  |  |  | |  |
| Informed consent | | x |  |  |  |  |  |  | |  |

1. 150µl to be administered in each nostril
2. DTH skin reaction; to be registered at 48 hours after immunization.
3. Body weight, height (at baseline only), blood pressure, heart rate, concomitant disease, concomitant medication
4. Hb, CRP, WBC (incl. diff), Platelets, Creatinine, Na, K, AST, ALT, LDH, ALP, -GT, Albumin, Total Bilirubin, Beta2-microglobulin. In addition, the subjects HLA type can be registered.

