### Dosage and administration of study drug

Vacc-4x is administered intranasal as a mixture of Vacc-4x peptides and the adjuvant Endocine.

The study includes four groups:

***A low dose group***: 80 µg Vacc-4x (20 µg pr. peptide) divided into two administrations;

40 µg Vacc-4x in 150 µl Endocine for each nostril.

***A medium dose group***: 400 µg Vacc-4x (100 µg pr. peptide) divided into two administrations;

200 µg Vacc-4x in 150 µl Endocine for each nostril.

***A high dose group***: 1200 µg Vacc-4x (300 µg pr. peptide) divided into two administrations;

600 µg Vacc-4x in 150 µl Endocine for each nostril.

***A zero dose group***: Only adjuvant divided into two administrations;

150 µl Endocine for each nostril.

The drug will be administered four times with one week interval; at week 1, week 2, week 3 and week 4.

A DTH test (Vacc-4x 400 µg intra-dermal) will be done at week 8.

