### Preparation of study drug

The preparation of study drug; Vacc-4x and Endocine should be performed by the study site pharmacist (or other responsible person). The date (DD/MM/YYYY) and time (XX: XX [24 hours]) of reconstitution should be recorded. The reconstituted product should be used as soon as possible after preparation. Due to instability of the Vacc-4x peptides, the final vaccine formulation will be mixed in connection with the administration to the subjects participating in the study. The stability of the final vaccine formulation has been tested by physiochemical stability testing of the emulsion. No changes were seen during the 12 hour observation period.

Vacc-4x is to be reconstituted with sterile Water for Injection (without preservative), United States Pharmacopoeia (USP) or European Pharmacopoeia (Eur Pharm).

The dose of Vacc-4 peptide is 80 µg, 400 µg and 1200 µg, respectively. After reconstituting, the peptide solution is mixed with the Endocine adjuvant at a 1+1 ratio and subsequently administered to the subject with 150 ul into each nostril (total 300 ul).

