# Study Procedures

## Time and events schedule

The study procedures to be conducted for each subject are divided into the following study phases: Screening (up to 4 weeks), Treatment Period (4 weeks), Follow-up Period (4 weeks).

The procedures to be completed during each of these phases are presented in the Study Flow Chart (Section 4.1, Table 2). Detailed descriptions of the assessments and the definition of study endpoints are provided in Section 8 (Study Assessments and Measurements). Any deviation from study procedures should be noted in the source documents and significant deviations should be reported to the Investigational drug substance suppliers immediately.

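### Visit 4 (Week 3, Day 15) orders study drug by intradermal injection, although the rest of the protocol gives every immunization intranasally

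*Protocol*

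**What the plan says.** The Visit 4 list in Protocol section 7.3.2 includes the step "Administration of study drugs via intradermal injection". The corresponding step at Visit 3 is "Administration of study drugs via intranasal administration", and Visits 2 and 5 carry the same nasal wording.

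Elsewhere the route is consistently nasal:

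- Section 3.1.1 sets the primary objective: to "evaluate the safety of intranasal administration of Vacc-4x with Endocine as adjuvant at three different dose levels".
- Section 4.1, Table 2, has a footnote to the immunization row, which covers all four dosing weeks: "150µl to be administered in each nostril".
- Section 6.1.2 states: "Vacc-4x is administered intranasal as a mixture of Vacc-4x peptides and the adjuvant Endocine".
- Section 6.3.3 says the prepared mixture is "administered to the subject with 150 ul into each nostril (total 300 ul").
- Section 7.1 ties the visit procedures to Table 2: "The procedures to be completed during each of these phases are presented in the Study Flow Chart".

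The only intradermal procedure planned in this trial is the Week 8 DTH skin test (sections 6.3.4 and 8.2.1). It is an assessment, uses 0.1 mL of Vacc-4x, and contains no Endocine.

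**The concern.** The visit lists are the instructions staff work from, and this one names the wrong route in a trial whose subject is the route. A nasal dose at Visit 4 departs from section 7.3.2, and an intradermal dose departs from section 6.1.2, so neither complies with the whole protocol. That also blurs what counts as a major violation for the per-protocol set in section 11.3.

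The line is not absurd on its face. Vacc-4x had previously been given intradermally (sections 2.1 and 2.6), section 6.1.3 aligns the dose and schedule with earlier studies, and the site needs staff able to give intradermal injections for the DTH test.

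If the line were followed, two things would be at stake:

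- **Subject safety.** Endocine would be injected into the skin, in the adjuvant-only arm as well. Both rat toxicology studies of Endocine cited in section 2.5 used nasal administration.
- **The primary objective.** Safety data after Day 15 would reflect a mixture of routes in the affected subjects, and their Week 8 T-cell and DTH results could not be attributed to nasal delivery.

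**Working it through.** The protocol states no figure to reproduce. The check is a comparison of text, followed by simple counts.

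**Route at each place**

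| Place in Protocol | Route of study drug |
| --- | --- |
| 3.1.1 Primary objective | intranasal |
| 4.1 Table 2, immunization footnote | each nostril |
| 6.1.1 Drug description, 6.1.2 Dosage | intranasal |
| 6.3.3 Preparation | each nostril |
| 7.3.2 Visit 2 (Week 1) | intranasal |
| 7.3.2 Visit 3 (Week 2) | intranasal |
| 7.3.2 **Visit 4 (Week 3)** | **intradermal** |
| 7.3.2 Visit 5 (Week 4) | intranasal |

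The remaining mentions of intradermal use concern earlier Vacc-4x studies, nonclinical work or the DTH test. None supports an intradermal immunization at Week 3.

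**Can the line be carried out?** The prepared dose is 2 × 150 µl = 300 µl, peptide mixed 1+1 with Endocine. The one intradermal procedure described uses 0.1 mL = 100 µl of peptide alone. No injection volume, site or technique is given for an immunization.

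**Doses exposed to the error.** Inputs: 24 subjects (section 4.1) and 4 doses each (section 6.1.2).

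- Planned doses: 24 × 4 = 96.
- Visit 4 doses: at most 24 × 1 = 24, and 24/96 = 25%.
- Doses before Visit 4: 24 × 2 = 48, all nasal.
- Range: 0 to 24 of 96, or 0% to 25%.

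**Follow-up time in an affected subject** (nominal final visit, Day 50)

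- Day 1 to Day 15: 14 days, intranasal only.
- Day 15 to Day 50: 35 days, mixed routes.
- Total: 14 + 35 = 49 days, so 14/49 = 29% and 35/49 = 71%.

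**Scheduled safety measurements.** Section 3.2.1 lists "Clinical laboratory evaluations (clinical chemistry, hematology) at screening, week 1, week 4 and week 8 (Termination"), and viral load, physical examination and vital signs follow the same schedule. The Week 1 blood samples and vital signs are taken before the first dose, and the physical examination precedes it in the Visit 2 order. That leaves two post-dose time points, Weeks 4 and 8, and both come after Visit 4. An affected subject therefore has 0 of 2 such time points under intranasal-only exposure. Adverse events with onset before Day 15 remain intranasal only.

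**The case against.** The strongest reply is that the document resolves its own conflict. One phrase stands against the title, the objective, the rationale, the dosing and preparation sections, the flow chart and three other visits. Staff would already have given the subject two nasal doses, and a 300 µl preparation made for two nostrils, with no injection instructions, would prompt a query. The trial has a single centre, enrols sequentially, and has full source verification (section 10.1) and monitoring against the protocol (section 12.7). The same error in all 24 subjects is therefore remote. Adverse events carry onset dates and times, and nasal application-site reactions are reported specifically, so part of the safety information could be separated by route. The split by days is a share of the calendar, not of events or information.

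Most of this stands, and it bears on likelihood: the upper end of the range is improbable, and confounding would be confined to affected subjects. It does not make the line correct. Monitoring and source verification find a deviation after the dose has been given. The two-week safety evaluation before the next dose level, if counted from a subject's first dose, falls at about Day 15, too early to show the effect of a Visit 4 dose. Dates and site-specific reporting cannot separate systemic events after Day 15, the Week 4 and Week 8 laboratory results, or the Week 8 immune responses.

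**Conclusion.** The concern holds. The Visit 4 dosing step contradicts every other statement of the immunization route and is wrong as written. The possible extent is 0 to 24 of 96 doses. The upper end assumes that all 24 subjects reach Visit 4 and that staff follow this line over the flow chart and dosing sections. The protocol gives no basis for a probability; the clarity of the other sections suggests the low end. Even one misrouted dose would be an exposure to intradermal Endocine that the protocol does not support, and would remove that subject's scheduled post-dose measurements from a clean evaluation of nasal safety. Because this is a route error in an operative dosing instruction and the remedy is trivial, it must be corrected despite the low likelihood.

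**What to change.** In section 7.3.2, Visit 4, replace the words *intradermal injection* with *intranasal administration*, matching Visits 2, 3 and 5. Check the site worksheets, CRF and pharmacy instructions for the same wording before the first subject reaches Day 15. Those documents are not available here, and nothing shows that they repeat the error. The cost is a one-phrase correction through the amendment procedure in section 12.2 and a note to the site, with no additional patients and no change to the analysis. With the correction, 0 of 4 doses per subject are assigned to the wrong route.

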#### Visit 5 (Week 4 – Day 22 (1))

The following procedures will be performed in the following order (it is important that all blood samples are taken before drug administration):

- Review of concomitant medications and AEs
- Physical examination, including weight
- Vital signs
- Clinical chemistry and hematology
- Viral load (HIV-1 RNA) and CD4 counts
- T-cell responses
- Collection of mucosal secretions
- Administration of study drugs via intranasal administration

The subject should remain in the clinic for 30 min after the administration of study drug to be monitored for adverse reactions to the immunization.

### Follow‑up period

The follow-up period consists of a 4-week period following the Week 4 visit.

#### Visit 6 (Week 8 – Day 50 (3)) – END OF STUDY

The following assessments will be performed:

- Review of concomitant medications and AEs
- Physical examination, including weight
- Vital signs
- Clinical chemistry and hematology
- Viral load (HIV-1 RNA) and CD4 counts
- T-cell responses
- Collection of secret from nose and rectum
- Collection of urine
- DTH test (immunization to occur on designated day; test to be evaluated 48 hours after immunization)

The subject should remain in the clinic for 30 min after the administration of the DTH test to be monitored for adverse reactions to the DTH test.

#### Visits 7 (Week 28), 8 (Week 52) and 9 (Week 76) (exploratory endpoints)

Post-study follow-up (T cell responses in blood and/or mucosal secretions): At 6 months interval Week 28 (pending documented immunogenicity week 8 in Vacc-4x group), Week 52 (pending documented immunogenicity Week 28 in Vacc-4x group) and final Week 76 (pending documented immunogenicity Week 52 in Vacc-4x group):

The following assessments may be performed:

- T-cell responses
- Collection of secret from nose and rectum
- Collection of urine
- Viral load (HIV-1 RNA) and CD4 counts

## Early withdrawal visit

Subjects may elect to discontinue from the study (i.e., withdraw consent for additional study follow-up) at any time. Every effort will be made to have the subject return to the clinic for a terminal evaluation.

## Subject discontinuation (lost to follow‑up)

In the event that a subject elects not to return to the clinic for the final study visit (Termination), the investigator must make every effort to contact the subject to review all AEs and collect study data. In the event that a subject drops out of the study at any time, the reason for discontinuation must be fully documented in the source documents and the CRF. The site personnel will document the AEs and any other assessments in the source documents and will make every effort to complete all required end of study assessments.

# Study Assessments and Measurements

## Demographic and screening assessments

The following demographic information and baseline characteristics will be collected at the screening visit:

- Date of birth
- Gender
- Ethnic origin
- Physical examination including height (measured in cm). Height measurement may also be obtained at Visit 2.
- Medical/surgical history (including current disease, pre‑ART CD4 counts, and pre‑ART HIV-1 viral load)
- Medication history
- HLA type (will be tested based on blood sample taken at visit 2)
- Vital signs (including blood pressure and heart rate)
- HIV-1 disease status as measured by viral load and CD4 counts
- ART medications and confirmation of clinically stable on the current ART regimen
- Clinical chemistry and hematology

## Efficacy assessments

### Delayed type hypersensitivity test administration

DTH testing will be performed at the last visit (Week 8). An injection of 0.1mL of a 4.0mg/mL Vacc‑4x should be administered intradermally at the front of left arm. The DTH test should be performed by the investigator, study nurse, or other clinician experienced in the techniques of intradermal injection. The DTH test results will be evaluated 48 hours after the tests are performed. For each DTH test, evaluation of the injection site at 48 hours will include palpable skin induration and skin erythema. A positive DTH test is defined as an area 10mm2 (either induration or erythema). Study personnel will record DTH results in the subject’s source documents and transcribe them into the CRF. For subjects whose DTH reactions are measured by someone other than study personnel, the investigator is responsible for collecting and recording the result; use of a prepared form completed by the alternative evaluator at the time of the reading is strongly recommended and should be filed with the subject’s source documents.

### CD4 counts

A blood sample (approximately 5mL) will be collected in tubes containing EDTA at Screening and Weeks 1, 4, and 8 (Termination). Tests will be performed at the local hospital laboratory.

### T-cell response

Blood samples (approximately 30 mL) will be drawn and the peripheral blood mononuclear cells (PBMC) separated. The PBMC will be frozen at -150°C, optionally will a fraction of fresh PBMC be tested. T-cell response to the Vacc-4x peptides will be measured in vitro by T cell activation assays (proliferation, cytokines) using flow cytometry (see assay [(Kvale, 2005)](#Kvale2005) and/or ELISPOT. Optionally, proinflammatory and inhibitory cytokines as well as tests for cytotoxicity (degranulation, secretion of Granzyme B or equivalents). T-cell proliferative responses will be compared with data reported in the preceding study CTN B-HIV-2/2002.

### Exploratory analyses

Time dependent change in Vacc-4x specific T cell responses: Provided that changes in T cell-responses to Vacc-4x can be achieved between study baseline and end-of-study by this new immunization methodology, as detected by new enhanced proliferative response and fraction of Vacc-4x-specific T cells in blood (activation-related cytokines such as IFN-, IL-2, TNF- as well as degranulating CD8+ T cells –producing), explorative analysis of the effects of each immunization will be of considerable interest. At present, no optimal vaccination schedule for T cell-dependent has been described in this new area of research.

Humoral responses to Vacc-4x in blood, mucosal sites and urine: Provided that changes in humoral responses in blood to Vacc-4x can be achieved between study baseline and end-of-study, exploratory analysis of samples from blood, mucosal fluid from rectum, vagina (optional) and urine may reveal the dose- and vaccination schedule-dependence in the development of such antibody responses.

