## Determination of sample size

It is decided that 6 subjects should be included in each of the four study arms. As this is a pilot study, the sample size has primarily been determined to provide descriptive statistics for the safety and efficacy parameters.

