## Statistical methods

Analyses will be based upon an intent-to-treat approach. In general continuous variables will be described using number of observations (N), mean, median, standard deviation (SD), minimum (min), maximum (max), Categorical data will be presented using counts (N) and percentages (%). Subjects without a baseline or a post-baseline assessment for a particular endpoint will not be included in the analysis of change from baseline for that endpoint. All statistical analyses will be performed using SAS Software Version 9.2 or higher. P-values will be reported as 2-sided p-values. All confidence intervals will be reported using traditional 95% two-sided intervals. No adjustment for multiple comparisons will be made.

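### Three exploratory analyses are weakened: mucosal and urine antibody work waits on a blood response, Week 2–3 T-cell samples are listed after dosing, and Weeks 28–76 have no Vacc-4x-naive arm

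*Protocol*

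**What the plan says.** **Mucosal and urine antibodies.** Protocol Section 8.2.4 opens its humoral paragraph with "Provided that changes in humoral responses in blood to Vacc-4x can be achieved between study baseline and end-of-study, exploratory analysis of samples from blood" and goes on to rectal fluid, optional vaginal fluid and urine. It does not mention nasal fluid. Section 3.1.3 sets the mucosal response (nose, rectum, optionally vagina) as an objective of its own, with no condition. Table 2 in Section 4.1 schedules mucosal secretions at Weeks 1, 4 and 8 and urine at Weeks 1 and 8 for all subjects. Visit 6 in Section 7.3.3 names nose and rectum.

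**T-cell kinetics.** In Section 7.3.2 the lists for Visits 3 and 4 are headed as a fixed sequence. In both, "T-cell responses (optional" is the last item, after study drug administration. At Visit 5 "it is important that all blood samples are taken before drug administration", and Visit 2 says the same. The notes to Table 2 make the Week 2 and 3 samples optional, depending on responsiveness.

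**Late follow-up.** Section 6.1.2 describes all four groups, the zero dose group included, and then states: "A DTH test (Vacc-4x 400 µg intra-dermal) will be done at week 8". Section 7.3.3 makes the first late visit conditional: "Week 28 (pending documented immunogenicity week 8 in Vacc-4x group". Weeks 52 and 76 each depend on the visit before.

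**The concern.** Each fault touches a different exploratory question.

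- The trial tests a mucosal route. An antibody response at the mucosa without one in serum is a result it should be able to see. If the blood result decides whether the mucosal samples are analysed, that pattern is missed by construction.
- Section 8.2.4 wants the effect of each single immunization. That needs samples taken at the same point relative to the dose. It also needs the Week 2 and 3 blood to exist, and blood not drawn then cannot be recovered.
- A response at Week 28 or later would naturally be read as persistence after the intranasal course. By then every subject has also had Vacc-4x by intradermal injection, including those meant to show what happens without it.

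**Working it through.** **1. Mucosal and urine samples: condition against schedule.**

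| Item | Sections 3.1.3 and 3.2.3 | Table 2 and visit lists | Section 8.2.4 |
|---|---|---|---|
| Nasal fluid | In the objective, unconditional | Collected; nose named at Visit 6 | Not listed |
| Rectal fluid | In the objective, unconditional | Collected; rectum named at Visit 6 | After a change in blood |
| Urine | Objective and endpoint, unconditional | Weeks 1 and 8 | After a change in blood |

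Collection is unconditional; only the analysis is conditional. Dropping the condition therefore adds assays and no visits. With 24 subjects, and assuming full attendance and both nose and rectum sampled each time, the upper limit is 24 × 3 × 2 = 144 mucosal samples plus 24 × 2 = 48 urine samples, before any vaginal samples.

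**2. T-cell samples: position relative to the dose.**

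| Time point | Status in Table 2 | Listed relative to that day's dose | Intranasal doses already given at the draw, as listed | If all draws were pre-dose |
|---|---|---|---|---|
| Screening | Mandatory | No dose | 0 | 0 |
| Week 1 | Mandatory | Before | 0 | 0 |
| Week 2 | Optional | After | 2 | 1 |
| Week 3 | Optional | After | 3 | 2 |
| Week 4 | Mandatory | Before | 3 | 3 |
| Week 8 | Mandatory | No intranasal dose | 4 | 4 |

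As listed, no sample follows exactly one dose, and Weeks 3 and 4 both follow three. The four mandatory time points still give a coarse course: baseline twice, after three doses, and after four.

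On timing, Section 8.2.4 defines the qualifying response as a change from baseline to end of study. Visit 6 is nominally Day 50, while Visits 3 and 4 are Days 8 and 15. The deciding result therefore comes 50 − 8 = 42 and 50 − 15 = 35 days after the draws it is meant to trigger. The sequential design does not clearly help, because Section 4.1 starts the next dose level after a two-week safety evaluation, well before the first subjects reach Week 8.

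**3. Vacc-4x exposure before Week 28.**

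The DTH dose reproduces. Sections 6.3.4 and 8.2.1 give 0.1 mL at 4.0 mg/mL, and 0.1 × 4.0 = 0.4 mg = 400 µg, as Section 6.1.2 states.

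Cumulative intranasal dose is four times the visit dose: 4 × 0 = 0, 4 × 80 = 320, 4 × 400 = 1600 and 4 × 1200 = 4800 µg. Before the DTH test the Endocine arm is the only arm at zero. After it, no arm is.

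**4. The trigger for late visits.** Section 3.2.3 does not say whose immunogenicity counts. Section 7.3.3 refers to the Vacc-4x group at all three visits, and the synopsis does so for Week 28 only. There are three Vacc-4x arms of 6, so the phrase could mean one arm or all 18 subjects. As an illustration, assume that one responder suffices and the response rate is p. Then P(triggered) = 1 − (1 − p)^n. For p = 5%, 10%, 20% and 30%, this is 0.27, 0.47, 0.74 and 0.88 with n = 6, and 0.60, 0.85, 0.98 and 0.998 with n = 18. The protocol gives neither p nor a threshold, so these figures show only that the unit matters.

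**The case against.** The best reply is that all of this is exploratory, in a pilot of 24. Section 11.1 says: "As this is a pilot study, the sample size has primarily been determined to provide descriptive statistics for the safety and efficacy parameters". That stands and limits the weight of the point. Thresholds for a response can also be left to an analysis plan, so their absence is not counted here.

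On the mucosal analysis, the sentence in Section 8.2.4 can be read as describing what might be learned, not as forbidding assays without a blood response. Sections 3.1.3 and 3.2.3 carry no condition. That reading is possible, but it leaves Section 8.2.4 at odds with the objectives, and its conditional opening will be read as a gate unless corrected.

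On kinetics, Section 8.2.3 and the Table 2 notes provide for freezing cells, so assays can be chosen later. This helps only if blood is drawn, and the notes call the samples themselves optional. It is also fair that a draw shortly after a dose probably reflects mainly the earlier doses; the documents have no data on this.

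On late follow-up, the protocol calls these visits post-study and promises no comparison with Endocine there. Section 7.3.3 does not exclude controls, and persistence within a subject can still be described. All of that stands.

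A reader might infer two stronger things. One is that these endpoints cannot answer their questions at all; the mandatory T-cell samples and unconditional mucosal collection contradict that. The other is that the DTH test contaminates the arms in proportion to dose, since 400 µg is 125%, 25% and 8.3% of the three cumulative intranasal doses. Those ratios divide intradermal by intranasal micrograms. The documents give no basis for equating the routes, so they do not measure immunological influence. Nor is there reason to think Visit 6 samples follow the DTH injection: it is listed last, although that list is not headed as a sequence.

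**Conclusion.** The point holds in a limited form: three exploratory analyses are weakened and none is voided.

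- **Mucosal and urine:** as worded, analysis depends on a different compartment from the one in the objective, and nasal fluid is missing from the list. This is the most consequential of the three. It rests on reading the opening of Section 8.2.4 as a condition.
- **Kinetics:** the sampling order at Visits 3 and 4 conflicts with Visits 2 and 5, and the stated trigger cannot be known when the blood is due. Two of six T-cell time points are affected, both optional.
- **Weeks 28–76:** no Vacc-4x-naive comparator remains. Late responses can be described, but not attributed to the intranasal course alone.

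The primary safety objective and the Week 8 T-cell, CD4 and DTH endpoints are unaffected. The repairs are cheap and should be made, and the second is lost for any subject who has passed Visits 3 and 4.

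**What to change.** 1. **Section 8.2.4:** remove the dependence on a blood response and add nasal fluid. Analyse the scheduled nasal, rectal and optional vaginal samples at Weeks 1, 4 and 8, and urine at Weeks 1 and 8, in all arms. The cost is extra assays on samples already collected.
2. **Section 7.3.2, Visits 3 and 4, and the Table 2 notes:** reconcile the order so that T-cell blood is drawn before dosing, as at Visits 2 and 5. Draw and freeze it in every subject, so that only the assay depends on the Week 8 result. The cost is two draws of about 30 mL per subject, already foreseen as optional.
3. **Weeks 28–76:** describe results as responses after the intranasal course plus the DTH injection. Reconcile the trigger wording in the synopsis and Sections 3.2.3 and 7.3.3, and state whether it applies to a subject, an arm or all Vacc-4x subjects. Recalling every subject in all four arms would be more informative, but it is a question of resources and not required. The cost is wording only.
4. **While editing:** one line can confirm that Visit 6 samples precede the DTH injection. Section 12.4 (data collection to Week 8) should be squared with the later visits. The route given at Visit 4 (intradermal) contradicts Section 6.1.2 (intranasal) and must be reconciled, since it bears on how the course is described.
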